### Statistical analyses

The planned statistical analysis for each phase: Data collected will be computed and analyzed using IBM Statistical Package for Social Science (SPSS) version 22.0 to produce the study results. Descriptive analyses using the mean and the standard deviation will be used to examine the data obtained. Descriptive statistics will be used to analyse the demographic data of every subject at their baseline. A box plot graph will be used to portray the distribution of data for example age, gender, year of study, area of study, and physical activity level.

The distribution of data will be analysed using normality of distribution. Mixed design analysis and intention-to-treat analysis will be used to assess the efficacy of aerobic training.

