### Study goal and objective

If an earlier, migraine is left untreated or undiagnosed, it is reported that around 2.5% of individuals with migraine are considered to have a chronic condition, defined as presenting with more than 15 headache days within a month. Subclassifications of the disease (migraine with and without aura and chronic migraine) occur clinically at various severity levels and coexist with numerous comorbidities. For this reason, several studies encourage a multidisciplinary and tailored treatment approach for these patients [26,27]. This preliminary randomized control trial aims to analyse the effectiveness of aerobic training among university students with migraine symptoms. The main objective is to determine the preliminary effect of aerobic training on migraine pain level, sleep quality, quality of life, and resting-state brain waves compared with EMG biofeedback training and placebo.

The alternative hypothesis of this study will be the aerobic training will be superior to EMG biofeedback training and placebo group in improving migraine pain level, sleep quality, quality of life, and resting-state brain waves. The null hypothesis will be the aerobic training is same as to EMG biofeedback training and placebo group in improving migraine pain level, sleep quality, quality of life, and resting-state brain waves. Although the Migraine Research Foundation listed three main types of non-drug treatments for migraine: lifestyle advice, therapies, and exercises. Some common aerobic exercises such as walking, jogging, a behavioral weight loss program, cycling, and a combination of cross-training, walking, jogging, and cycling are suggested to be beneficial to migraine patients but there remains no specific protocol established till now. Hence, this study will contribute to the research field by establishing an aerobic training protocol for patients with migraine symptoms.

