### Sample size

Sample size is calculated based on migraine, biofeedback training [29] and aerobic training articles [30]. Using g power statistical tool F test, ANOVA: repeated measure, between factors, and with 0.4 effect size, 0.05 alpha error, 0.95 beta error, 3 groups, 4 outcome measurements the sample size is 66. Then, further adjustment of sample size to accommodate 25% dropout rate [31] gives the final estimated value to 88.

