### Randomization

A simple random sampling method will be employed as the sampling technique in recruiting the subjects. Upon successful recruitment of participants, and with Migraine Disability Assessment Scale (MIDAS) Questionnaire, the subjects will be allocated into either of the three groups (Group 1: aerobic training, Group 2: biofeedback training, Group 3: placebo group). The subjects will be given a random number in an excel sheet and ranked. Following ranking, the ranked participant will be divided by size and group accordingly.

Simultaneously using MIDAS, each group will have 7–10 participants depending on each level of disability on MIDAS. In the Migraine Disability Assessment Scale (MIDAS) Questionnaire that assesses headache-related disability, the respondents are required to answer five questions. The number of days in each question will be summed up and the scoring indicates the activity limitation due to migraine in the past 3 months. The participants are then categorized into no or little disability (0–5), mild disability (6–10), moderate disability (11–20), and severe disability (21+) (Stewart et al., 2001).

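### The hypothesis is that aerobic training beats each of two comparators, but the only test named and powered is a three-group F test; baseline and MIDAS level could also be better used

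*Protocol article*

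**What the plan says.** - **Hypothesis** (Study goal and objective): "The alternative hypothesis of this study will be the aerobic training will be superior to EMG biofeedback training and placebo group", for pain level, sleep quality, quality of life and resting-state EEG. This is a directional claim against two comparators.
- **Sizing test** (Sample size): "Using g power statistical tool F test, ANOVA: repeated measure, between factors", with "0.4 effect size", "0.05 alpha error", 0.95 (printed as beta error, evidently power), 3 groups and 4 measurements. The result is 66, and "further adjustment of sample size to accommodate 25% dropout rate" brings it to 88.
- **Efficacy analysis** (Statistical analyses): "Mixed design analysis and intention-to-treat analysis will be used to assess the efficacy of aerobic training". No contrast between named groups is given.
- **Measurement times** (Methodology): two, baseline and week 6.
- **Allocation** (Randomization): "each group will have 7–10 participants depending on each level of disability on MIDAS", over four disability levels. The confounders listed under Outcomes are pain level, gender, age and COVID-19. MIDAS is not among them, and the analysis section does not mention it.

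**The concern.** The hypothesis and the named test answer different questions. A three-group F test has no direction and does not single out aerobic training. It can be significant because biofeedback differs from the other two groups, or because aerobic training does worse. If such a result were reported as efficacy of aerobic training, the conclusion could be wrong. The 95% power attached to that test would also be read as the chance of confirming the hypothesis, which it is not.

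Two smaller points concern precision. With one baseline and one follow-up value, the group-by-time test of a mixed design is a comparison of change scores. That is valid under randomisation but less precise than conditioning on baseline. And the factor used to balance the groups is not carried into the analysis as described.

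**Working it through.** **Inputs.** From Sample size: f = 0.4, alpha 0.05, power 0.95, 3 groups, 4 measurements, N = 66 completers. From Methodology: 2 measurement times. Assumed: equal groups (22 each), and a correlation rho between repeated values, for which the protocol gives no figure. I use 0.5 and show 0.3 and 0.7.

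**1. The plan's own figure.** For the between-groups test, lambda = f²·N·m/(1 + (m − 1)rho), with 2 and N − 3 degrees of freedom. With m = 4 and rho = 0.5:
- N = 66: lambda = 0.16 × 66 × 4/2.5 = 16.9, power 95.8%.
- N = 63: power 94.9%.

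So 66 is reproduced, and 66/0.75 = 88. The 95% therefore belongs to the omnibus main effect of group, averaged over times. If the groups differ only at week 6, that average halves the effect to f = 0.2. With the two times actually measured, lambda = 0.04 × 66 × 2/1.5 = 3.52 and power is 36%. (The mismatch between 4 measurements and 2 times is a separate matter.)

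**2. Omnibus group-by-time test, effect only at week 6.** In units of the single-measure variance, the residual variance is 2(1 − rho) for the change score and 1 − rho² for ANCOVA. Lambda = 0.16 × 66 / variance = 10.56 / variance, with 2 and 63 degrees of freedom.

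| rho | variance, change | variance, ANCOVA | power, change | power, ANCOVA |
|---|---|---|---|---|
| 0.3 | 1.40 | 0.91 | 67% | 85% |
| 0.5 | 1.00 | 0.75 | 82% | 92% |
| 0.7 | 0.60 | 0.51 | 96% | 98% |

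At rho = 0.5 the ratio 1.00/0.75 = 1.33 means the change score needs about a third more participants for the same precision. Taking off 4 degrees of freedom (baseline and three MIDAS terms) moves the ANCOVA power at rho 0.5 from 0.917 to 0.916, with no credit for any variance that MIDAS explains.

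**3. What a significant F can mean.** Omnibus power depends on f, not on which group differs. If biofeedback alone works and aerobic training equals placebo, the change column applies unchanged: 67%, 82% or 96% of trials give a significant F with no aerobic effect.

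**4. The comparisons the hypothesis needs.** Two mean patterns give f = 0.4:
- A, aerobic differs from two equal comparators: d = 0.4 × 3/√2 = 0.85 against each.
- B, evenly spaced with aerobic best and placebo worst: range 0.4 × √6 = 0.98 against placebo, and half of that, 0.49, against biofeedback.

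The noncentrality is d/√(variance × 2/22), with 63 degrees of freedom and two-sided 0.05. At rho 0.5:

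| Comparison | change score | ANCOVA |
|---|---|---|
| A, aerobic vs each comparator | 79% | 89% |
| B, aerobic vs placebo | 89% | 96% |
| B, aerobic vs biofeedback | 36% | 46% |

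With the change score, over rho 0.3 to 0.7, the first row runs from 65% to 95% and the last from 27% to 54%. Where both comparisons must succeed, joint power cannot exceed the smaller of the two.

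**5. Multiplicity.** If either of two unadjusted 0.05 tests could carry the claim, the error rate is up to 1 − 0.95² = 9.75% (independence bound). If both must succeed, or the order is fixed in advance, no split of alpha is needed.

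**The case against.** The strongest reply is that one sentence in a journal article does not exclude planned contrasts. A mixed design can carry them, an analysis plan not shown may name them, and nothing says that the investigators would read an omnibus F as an aerobic effect without looking at the group differences. The trial also calls itself a pilot of preliminary efficacy. This stands against any claim that the design cannot test the hypothesis. It does not remove the mismatch, because the article itself fixes both the hypothesis and the sizing test, and they differ.

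A reader might infer three stronger things:
- **That participants with incomplete data are dropped, 22 of 88 at the planned dropout, despite intention-to-treat.** The documents do not say so. The sizing routine does not fix the analysis model, the mixed design may be an ANOVA or a likelihood model, and missing-data handling is commonly left to the analysis plan. Nor would a common-baseline mixed model recover these people: with one follow-up, those with baseline only add essentially nothing on group contrasts.
- **That baseline is ignored.** It is not. Baseline enters as a level of time, and the resulting change-score comparison is valid. ANCOVA is a gain in precision, not the repair of an error.
- **That leaving out MIDAS biases the result.** Omitting a balancing factor generally makes the test conservative rather than biased, and model terms are often left to the analysis plan. What stands is that the factor is known, used in allocation and cheap to include.

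**Conclusion.** The point holds as a mismatch between hypothesis and named test, with two secondary gains in precision. The omnibus F does not establish superiority over either comparator, and the 95% power does not apply to the pairwise claims. At rho 0.5 with 22 completers per group, those claims have 79% power each in the favourable pattern and 36% against biofeedback when the means are evenly spaced. Conditioning on baseline is worth about 10 percentage points of omnibus power at rho 0.5, 19 at rho 0.3 (66.8% to 85.5%) and 2 at rho 0.7.

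These sizes rest on an assumed rho, equal groups, f = 0.4 placed at week 6 only, and the two mean patterns shown. The logical point about the omnibus test needs none of them. This is a worthwhile correction to make before the data are analysed, not a flaw that invalidates the trial.

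**What to change.** 1. Analyse week-6 values with baseline as covariate, or the equivalent common-baseline mixed model, and with MIDAS level as a factor.
2. Base the conclusion on two planned contrasts, aerobic vs placebo and aerobic vs biofeedback. Either require both at 0.05, which matches the hypothesis as worded, or test them in that fixed order, each at 0.05. State which.
3. In Sample size, state that the 95% power belongs to the omnibus between-group test, and give the power of the two contrasts with the assumed correlation.

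**Cost.** Steps 1 and 2 change analysis wording and use data already collected. The extra terms cost a few degrees of freedom (power 0.917 to 0.916 at rho 0.5). The real price is a less favourable stated power, above all against biofeedback, where even ANCOVA gives 46% under evenly spaced means at rho 0.5.

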## Discussion

There is no specific test to diagnose migraine. For an accurate diagnosis, a general physician must identify the pattern and associated symptoms. Migraines can be unpredictable, sometimes occurring without symptoms. If underdiagnosed or over-looked, it encompasses a serious of long-term effects. "Studies show a dysfunctional learning process in the brain in migraine and in other pain conditions," Brennan says: "The brain learns to produce and perpetuate pain." In other words, migraine can teach the brain that pain is normal, so the brain changes to help pain happen more often [52]. The long-term comorbidities include cardiovascular disease, stroke, white matter lesions, hypertension, gene polymorphisms, cardiac disease, psychiatric disease, depression, diffuse anxiety disorder, panic disorder, and bipolar disorder [53], obesity. Thus, a non-pharmacological treatment becomes more evident to avoid polypharmacy or drug interactions [54].

Hence with appropriate intervention, the symptoms can be prevented from worsening. Evidence suggests the importance of psychological [5], behavioural [55], and surgical intervention [14]. But there is an unmet need for evidence-based non-pharmacological approaches to complement pharmacotherapy in migraine prevention [54]. On the other hand, some migraineurs report exercise as a triggering factor for their attacks [56]. Maybe this is one of the reasons for lacking evidence. In general, exercise can be used for the management of several chronic pain conditions [57]. Moreover, an exercise intervention may be more suitable for people with migraine considering their tendency toward inactivity [54]. The empirical support for recommending a specific exercise program for prophylactic treatment is relatively limited [54]. Hence this is the first study also aiming to establish an aerobic protocol for patients with migraine symptoms. The intervention proposed in this study is simple and would be easy to implement in a clinical setup provided it if shown to be effective. The failure of more intensive interventions may be due to lack of compliance [58]. Thus, this study chose an intervention level to achieve a high compliance rate.

Although some studies developed exercise programs for untrained patients with migraine, the outcome was primarily in terms of exercise capacity rather than the primary characteristics and secondary resting-state brain wave analysis/ sleep quality changes, indicating the need for this study. Additionally, these studies assessed the impact of drugs [27] indicating the need to assess the non-pharmacological importance to migraine patients. One of the expectations in this study is that the participants would also prefer to modify their existing lifestyle and thus will have several health benefits.
